### 2.19. Safety Evaluation

Given the nature and objectives of the study, there are no foreseeable adverse events related to the conduct of experimental activities. The only adverse effects to consider are related to the treatment that the involved patients will undergo. However, the likelihood of risks and side effects is low since no invasive treatments or therapies are planned. The devices are CE-marked and have been in use at some of the investigational centres since 2016, where they have been used to treat hundreds of patients and thousands of rehabilitation sessions. Furthermore, the treatment will always be supervised by experienced physiotherapists. In our experience and the literature, no adverse events have been reported. In any case, regarding any reportable events, the mode and timing of reporting will refer to the obligations imposed by EU Regulation 2017/745 (Article 80) and the MDCG Guideline 2020-10/1 (“Safety reporting in clinical investigations of medical devices under the Regulation (EU) 2017/745”).

### 2.20. Ethics and Dissemination

This study protocol (version 2, 29 May 2024) was reviewed and approved by the National Ethics Committee for Clinical Trials of Public Research Bodies (EPR) and other National Public Institutions (CEN) on 17 July 2024 (Prot. PRE BIO CE n. 0027276).

This trial collects personal data, including sensitive categories, as per Article 9 of the European regulation on the protection of personal data 2016\679 (General Data Protection Regulation or “GDPR”). The legal basis for data collection and processing is the informed consent of enrolled patients (Article 6 para. 1 letter a, and Article 9 para. 2 letter a GDPR) and the personnel involved in the questionnaires (Article 6 para. 1 letter a GDPR). The latter will only involve personal data as per Article 6 para. 1 of the GDPR, excluding sensitive data. Upon consent from the subject or their family/caregiver/guardian, data will be pseudonymised and then entered into a computerised database using the REDCap (Research Electronic Data Capture) application installed on an AWS Cloud space managed by the Information Systems of the University of Pavia. During the study, access to the registry will only be granted to the principal investigators of each experimental centre concerning the data of their reference centre. Collaborators accessing the computerised database will not be able to trace back the identity of the subjects in any way. Not even the sponsor will have access to re-identification keys, but will have access to all data entered in the REDCap registry [77]. Only the principal investigators of each centre will be able to trace back the identities of the enrolled participants at their own centre. The correspondence between the patient’s name and the associated ID will be kept in a protected external file, accessible only to the principal investigators of the individual recruitment centres for any clinical follow-up purposes. This file will be deleted once data collection is completed and the quality control of the collected data is carried out. Consequently, at the end of the database establishment, these data will be definitively anonymised by destroying the re-identification keys and potentially removing identifying combinations (for example, patient data linkage with the collection centre) as indicated in recital 26 of the GDPR. For this reason and in compliance with the principle of minimal data retention, they will be kept for 10 years after the conclusion of the study. Once the aforementioned retention period has expired, the data will be verified for the maintenance of anonymity and possibly kept anonymous so that it continues to be impossible, directly or indirectly, to trace back to the identity of the data subject. These data may thus be reused for subsequent research purposes under Article 89 GDPR and may therefore be retained indefinitely.

Regarding biological samples, for each patient, serum samples (aliquots) and whole blood tubes will be identified by reference ID and stored at −20 °C until shipment. All samples will be then transferred and analysed at the laboratory located at the Fondazione Don Carlo Gnocchi ONLUS “S. Maria della Provvidenza” Centre, Rome. Samples will be shipped to this laboratory according to specific procedures and maintaining a controlled temperature (dry ice shipment). The biological material will be utilised exclusively for research purposes related to the execution of the study, and it will be analysed only by the personnel of the above-mentioned Centre at Fondazione Don Carlo Gnocchi, Rome. The collected biological material will be stored under secure conditions and according to scientifically recognised procedures. The sample will be preserved with alphanumeric labelling not traceable to the individual patient. Biological data will be processed in accordance with the GDPR and the current national legislation (Legislative Decree 196/2003 and subsequent amendments), as well as the Deontological Rules for statistical or scientific research treatments published pursuant to Article 20, paragraph 4 of Legislative Decree 10 August 2018, No. 101—19 December 2018. In particular, the processing, with the aforementioned security measures, will take place in compliance with Article 9 of the Regulation, Article 2-sexies, the prescriptions identified by the Data Protection Authority pursuant to Article 21 of Legislative Decree No. 101 of 2018, and the specific safeguards adopted by the Data Protection Authority data pursuant to Article 2-septies of Legislative Decree 196/2003.

The research team plans to disseminate the trial findings at both national and international conferences, as well as publish them in international journals. Patient data collected during the trial will be anonymised and made available to the scientific community in accordance with principles of “Open Science” and “FAIR Data”.

### 2.21. Patients’ Enrolment Monitoring

In order to keep the information on patients’ enrolment by every centre up-to-date, a monitoring tool was developed using the REDCap platform. Each centre identified a responsible person who has given credentials for entering data for that centre. Each centre is periodically required to fill in a form reporting the number of patients enrolled so far, possible dropouts, and possible issues. The main objective of this dashboard is to allow the detection of criticalities as soon as possible, in such a way as to take corrective actions on time.

## 3. Discussion

Robotics and technology in the field of rehabilitation have been proposed as tools that can enhance the effectiveness of treatments. Early rehabilitation robots were specifically designed to increase the quantity and intensity of therapy, particularly for patients with severe motor impairments, while also reducing the workload on physical therapists. Traditionally, rehabilitation treatments rely on clinical staff to either assist or directly facilitate patients’ movements, which presents limitations in terms of time and human resources, often impacting treatment outcomes. An equally important advantage of using robots is their ability to provide objective measurements of motor performance. Equipped with sensors, these devices can collect objective data, such as kinematic or dynamic metrics, and generate precise indicators related to the biomechanics of a patient’s movements. When properly collected, these data offer a reliable assessment of the patient’s condition and allows for tracking progress over time.

Despite the potential benefits of using robots and technology in rehabilitation, several barriers hinder their widespread adoption in clinical practice. Although these technologies show promise in enhancing the measurement, intensity, and personalisation of rehabilitation treatments, their high costs—encompassing not only the purchase of the equipment but also the training required for practitioners—remain a significant challenge, along with legal and ethical considerations. Regarding the effectiveness of robotics and technology for post-stroke patients, the scientific literature includes numerous meta-analyses. However, these studies often yield inconclusive results due to various factors, notably the substantial variability in treatment duration, session frequency, and specific therapeutic approaches across different studies. Additionally, the small sample sizes in many studies pose challenges for evaluating overall efficacy. This underscores the need for pragmatic studies on larger, real-world populations, using a consistent treatment and measurement model while maintaining clinical feasibility within current regulatory frameworks. It is therefore essential to assess both the effectiveness and sustainability of these technologies in clinical practice through large-scale pragmatic trials to generate robust findings. For this reason, we have designed a pragmatic trial involving a broad sample of post-stroke patients in the subacute phase (within six months of the acute event).

To our knowledge, this is the first trial in the literature that will study the effectiveness of a multimodal, multidomain rehabilitation based on the use of robotics and allied technologies on such a large sample of subacute phase stroke patients. As mentioned, rehabilitation after a stroke is a comprehensive process involving all impaired functional domains, namely sensory-motor function of the upper limb (in the proximal and distal district), lower limb and gait, balance, and cognitive functions. Today, robots and technologies that can rehabilitate all four domains are available. Thus, unlike previous trials that evaluate the effect of a robot in one segment (upper limb or lower limb), this trial proposes a treatment model using a set of robots to treat up to four functions. In fact, our primary outcome is the patient’s ability in activities of daily living in which the use of the upper limb is fundamental both in its reaching component but also in the grasping of objects; similarly, in the skills of daily living, the function of gait and thus balance is fundamental; on the other hand, all these functions are strongly influenced by cognitive abilities (a patient with impaired attention and planning, for example, will have difficulty in performing complex movements).

Post-stroke rehabilitation is indeed a complex process involving the sensorimotor functions of the upper and lower limbs, cognitive functions, and language, impacting activities such as walking, balance, and autonomy. We consider it crucial to adopt a global approach oriented towards the recovery of all compromised sensorimotor as well as cognitive functions (14) because all these functions are closely interconnected. We decided to use daily living abilities as the primary outcome because we believe it is the most important goal of recovery after stroke that may summarise the four functional domains being treated. The secondary outcome measures were chosen according to the ICF because the ICF framework is a comprehensive and person-centred approach that utilises the concept of human functioning adopted by the World Health Organization. It is based on the idea that health is not just the biological state of the body but also the ability to take part in daily life and achieve personal goals.

The study aims to demonstrate the non-inferiority (and eventually, the superiority if non-inferiority is established) of rehabilitation treatment integrated with RADTs, compared to only traditional rehabilitation treatment in stroke patients in the recovery of daily life abilities. Secondary objectives include assessing the targeted domains (upper limb, lower limb, balance, cognitive functions) according to the ICF. Moreover, by analysing neurophysiological parameters and factors related to neuroplasticity, along with demographic and clinical data, we can deeply profile patients to identify the factors that predispose them to recovery.

The study also intends to assess the acceptability and usability of robot-assisted rehabilitation for both patients and healthcare providers, develop a predictive model to forecast the effectiveness of robotic treatment, and evaluate its economic and organisational sustainability. The ultimate goal is to provide crucial data to guide the large-scale implementation of robot-assisted rehabilitation in stroke patients, considering both clinical effectiveness and economic and organisational aspects. Finally, the data collected in the trial will be made available to the scientific community in accordance with the “Open science” and “FAIR Data”.

A limitation of the study is the use of different technologies across various research centres. However, this approach allows us to conduct a trial that more accurately reflects real-world conditions. Given the wide range of existing robotic and technical systems and the constant development of new ones, it is unlikely that all centres offering robotic rehabilitation for stroke patients would use the same technology. Had we standardised the technology across all centres, we would have faced challenges in recruiting a sufficient number of patients, as the number of centres with identical robotic systems within the Fit4MedRob Consortium is limited. More importantly, this would have compromised the generalizability of the results. To address the inevitable heterogeneity in the systems used to treat the experimental group, we precisely defined the functional domains that robotic or technological treatments must target, including the lower limb, balance, proximal and distal upper limb segments, and cognitive functions and, accordingly, the protocol of the robotic sessions (duration, repetitions, and rotation scheme).

Another potential limitation is the inclusion of traditional treatment alongside the specific sessions for each treatment arm (robotic or traditional). In the proposed experiment, patients in the experimental arm will receive both targeted interventions for the five functional domains using one or more robots per domain and traditional treatment. To address this, we ensured that patients in both treatment arms received the same amount of therapy: two daily sessions of traditional rehabilitation in the traditional group, one session of traditional rehabilitation, and one session of robotic rehabilitation daily in the robotic group. This design choice stems from our belief that traditional and robotic treatments are complementary rather than mutually exclusive. We are convinced that robotic devices cannot replace the expertise and proven effectiveness of traditional rehabilitation but can serve as valuable tools in the hands of skilled therapists, enabling more precise and personalised treatment.

It is important to note that this trial was designed based on the results of a survey conducted by the Fit4MedRob Consortium, which highlighted an urgent need for large-scale, pragmatic studies focusing on comprehensive recovery of sensorimotor and cognitive functions through a multidomain approach. The survey indicated that many patients require simultaneous rehabilitation across multiple functional domains, necessitating a shift from treating individual domains to adopting a holistic approach, in line with the World Health Organization’s concept of “human functioning.” Furthermore, developing sustainable and advanced therapies is crucial to providing effective rehabilitation with robotic systems in a cost-efficient manner for the National Health System.

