### 2.7. Randomisation

Patients will be randomly assigned either to a robotic–technological rehabilitation treatment or to a traditional rehabilitation treatment. The randomisation will be centralised, overseen by an experimenter not directly involved in patient recruitment, treatment, or evaluation, and will be stratified by clinical centre, time since stroke (inferior to 3 months; between 3 and 6 months), and clinical setting (inpatient or outpatient). Randomisation lists will be generated using the National Cancer Institute Clinical Trial Randomization Tool (https://ctrandomization.cancer.gov/).

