### 2.10. Intervention Schedule

Patients in the experimental/control group will undergo a total of 25 robot-assisted/traditional sessions, each lasting 45 min, with the following frequency:Five times a week for 5 weeks, for inpatients;Three times a week for 8.3 weeks, for outpatients.

The difference in treatment frequency between the two settings is related to current regulations and the difficulty as an outpatient to travel to urban rehabilitation facilities on a daily basis. This approach ensures that patients receive the same number of rehabilitation sessions and are able to attend all scheduled sessions, thus reducing the risk of potential dropouts.

In addition, according to current Italian regulations, which require providing inpatients with 3 sessions/day of treatment for 6 days/week, all inpatients (also those randomised in the intervention arm) will undergo, in addition to the 25 sessions, traditional rehabilitation sessions (neuromotor and occupational therapy, according to patient’s need) (6 times/week), lasting 45 min. To avoid the possibility of performance bias, the therapists who will treat subjects in RADT-assisted treatment will be different from therapists who will treat the same subjects traditionally. Moreover, according to the medical prescription, all subjects (inpatients and outpatients) will undergo one session/day of cognitive, occupational, speech, or swallowing therapy based on their needs. The intervention provided to patients in both groups, in inpatient and outpatient settings, is reported in Figure 3.

All rehabilitation sessions, including type (neuromotor, occupational, cognitive, occupational, speech, swallowing therapy), method (robotic or conventional), duration in minutes, and possible issues arising, will be recorded daily by the therapists (session diary).

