#### 2.18.1. Primary Analysis

The primary endpoint of the modified Barthel Index variation at the end of treatment will be compared between treatment groups using a mixed-effects linear model with the clinical centre as a random effect to obtain a corrected estimate of variance and, therefore, a correct confidence interval for the difference between the changes in the two groups. Non-inferiority will be assessed at a significance level of 2.5% by estimating the effect with a bilateral 95% confidence interval (CI) and comparing the lower limit of the CI with the non-inferiority margin of −5 points. For the analysis of the primary outcome, the mixed-effects model will initially be applied to the PP population. The analyses will be completed according to the Intention-To-Treat strategy [75,76], including all randomised subjects, along with a sensitivity analysis. The ITT population will be defined by assuming a follow-up, and therefore an evaluation of outcomes, on subjects who interrupt treatment. The analysis will be conducted assuming that missing data are “missing at random” (MAR); therefore, a mixed model for repeated measures will be applied, including all subjects in the analysis. With respect to the assumption of MAR, a sensitivity analysis will be performed considering scenarios deviating from it and involving one or both groups. Additionally, a sensitivity analysis will be used to assess additional adjustments for baseline modified Barthel Index values. If non-inferiority is concluded for the primary outcome, superiority can be evaluated without the need for correction for multiple comparisons. Regarding the primary outcome, an analysis of planned subgroups will be conducted to assess the presence of treatment effect modifiers, extending the models to include interaction terms between these factors and treatment.

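### The Discussion describes one daily therapy schedule for all patients, but section 2.10 gives the added traditional session to inpatients only, so the treatment contrast differs by setting, and the primary model does not name setting

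*Protocol article*

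**What the plan says.** All references are to the protocol article.

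- **Section 3, Discussion.** Traditional therapy given beside the arm-specific sessions is raised as a possible limitation. The answer is "To address this, we ensured that patients in both treatment arms received the same amount of therapy": two daily traditional sessions in the control group, and "one session of traditional rehabilitation, and one session of robotic rehabilitation daily in the robotic group". No setting is named.
- **Section 2.10, Intervention Schedule.** Each patient has 25 arm-specific sessions of 45 minutes. Inpatients have them five times a week for 5 weeks; for the others the schedule is "Three times a week for 8.3 weeks, for outpatients". The added traditional therapy, six times a week and 45 minutes each, is tied to inpatient regulations: "all inpatients (also those randomised in the intervention arm) will undergo, in addition to the 25 sessions, traditional rehabilitation sessions". Separately, "all subjects (inpatients and outpatients) will undergo one session/day of cognitive, occupational, speech, or swallowing therapy based on their needs".
- **Section 2.7, Randomisation.** Besides centre, the stratification factors are "time since stroke (inferior to 3 months; between 3 and 6 months), and clinical setting (inpatient or outpatient".
- **Section 2.18.1, Primary Analysis.** The change in the modified Barthel Index is compared "using a mixed-effects linear model with the clinical centre as a random effect", and the lower limit of one 95% CI is set against −5 points. Planned subgroups with interaction terms are announced, but their factors are not named.

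**The concern.** The Discussion sentence tells the reader what the trial compares. It describes a robotic arm that always keeps a parallel daily traditional session. Under section 2.10 that holds for inpatients and not for outpatients.

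This matters for two reasons.

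1. Equal session counts between arms deal with unequal dose. They do not deal with dilution: therapy shared by both arms can pull the difference towards zero, and in a non-inferiority trial that favours a pass. How much is shared depends on setting, so the two settings carry different contrasts.
2. The result is one pooled difference, weighted by an inpatient–outpatient mix that the article does not fix (enrolment is competitive, section 2.5). Read through the Discussion sentence, a pass driven mainly by inpatients would be taken to cover outpatients under the same regimen, which they do not receive.

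Setting was judged important enough to stratify on, but the stated primary model does not include it.

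**Working it through.** **1. The plan's own sample size (section 2.15).** Margin 5, SD 20, power 80%, one-sided 2.5%, true difference 0:

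n per arm = 2 × (1.960 + 0.842)² × 20² / 5² ≈ 251.2, so 252, or 504 in total, against 506 stated. A t-based calculation plausibly explains the gap of 2. With 15% dropout, 506 / 0.85 = 595.3, so 596, as stated. The present point does not alter these figures.

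**2. Can the Discussion sentence fit both settings?** Sessions in the robotic arm under section 2.10:

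| What counts as traditional | Inpatients | Outpatients |
|---|---|---|
| Added sessions only | 1 traditional + 1 robotic: fits | 0 traditional + 1 robotic, three days a week: does not fit |
| Added plus needs-based session | 2 traditional + 1 robotic: does not fit | 1 traditional + 1 robotic, but only on the three robotic days |

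Neither reading makes the sentence true of both.

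**3. Share of sessions switched to RADTs.** Arm-specific plus added traditional sessions:

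- Inpatients: 25 + 6 × 5 = 55; 25/55 = 45%.
- Outpatients: 25 + 0 = 25; 25/25 = 100%.

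Now add the needs-based session. The article does not say on how many days a week it is given, so a range is assumed:

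- Inpatients, 5 to 7 days a week for 5 weeks (25 to 35 sessions): 25/80 = 31% to 25/90 = 28%.
- Outpatients, 3 to 7 days a week for 25/3 = 8.33 weeks (25 to 58.3 sessions): 25/50 = 50% to 25/83.3 = 30%.

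The gap narrows, and it nearly closes if outpatients have this session every day.

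**4. What averaging can do (illustration only).** With 253 per arm, SE = 20 × √(2/253) = 1.778. For a pooled true loss d, P(pass) = P(Z > 1.96 − (5 − d)/1.778). Assume that outpatients truly lose 6 points, 1 beyond the margin. In the proportional case inpatients lose 6 × 25/55 = 2.73.

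| Outpatient share (assumed) | d, inpatients lose 0 | P(pass) | d, inpatients lose 2.73 | P(pass) |
|---|---|---|---|---|
| 20% | 1.20 | 57% | 3.38 | 15% |
| 30% | 1.80 | 44% | 3.71 | 11% |
| 50% | 3.00 | 20% | 4.36 | 5% |

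The article gives neither the mix nor these losses.

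**5. Precision by setting.** For outpatient share q, the outpatient half-width is 1.96 × 20 × √(2/(253q)); for inpatients, replace q by 1 − q. SD 20 is assumed in each setting.

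| q (assumed) | Outpatient half-width | Inpatient half-width |
|---|---|---|
| 20% | 7.8 | 3.9 |
| 30% | 6.4 | 4.2 |
| 50% | 4.9 | 4.9 |

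**The case against.** The strongest reply is that the operative schedule is not in doubt. Section 2.10 sets it out by setting, and the Figure 3 caption says that the figure does the same. One loose Discussion sentence would not change how any site treats a patient. This stands: the error is in how the trial is described, not in how it is run.

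Three stronger readings are tempting, and the documents do not support them.

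- **That outpatients in the robotic arm keep no traditional therapy.** Section 2.10 gives every patient a needs-based daily session, and section 2.9.2 counts cognitive rehabilitation among traditional methods. The 25 of 25 concerns arm-specific plus added traditional sessions only.
- **That the Discussion contradicts itself by saying "robotic devices cannot replace the expertise and proven effectiveness of traditional rehabilitation".** The sentence goes on to call robots tools for skilled therapists. It states a belief that the two are complementary and makes no claim about how many sessions are swapped.
- **That pooling the settings is itself an error.** Session numbers are balanced between arms within each setting, and allocation is stratified by setting, so setting does not confound the pooled difference. One average effect over a natural case mix is an ordinary target for a pragmatic trial.

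Two further objections hold in part. Subgroup factors are commonly left to the analysis plan, which is not shown, so their absence here is no fault. That does not correct the Discussion sentence, nor does it alter a stated primary model that names only centre. It is also true that a main effect of setting still yields one pooled difference; only the interaction shows the difference by setting.

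Finally, the pass probabilities rest on assumed inputs. If losses follow the share of sessions switched, the pooled test usually fails, as it should; the higher figures need inpatients to lose nothing.

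**Conclusion.** The point holds as a misdescription with a modest consequence for analysis and interpretation. The Discussion's single schedule cannot be true of both settings. RADTs replace 45% of arm-specific plus added traditional sessions in inpatients and all of them in outpatients, or about 28–31% and 30–50% with the needs-based session under the assumed frequencies. The contrast therefore differs by setting. The pooled estimate remains valid but averages over that difference, and equal session counts answer only the question of dose.

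Separately, setting is a stratification factor that the stated primary model leaves out. Section 2.11 links setting to clinical severity, so it is probably prognostic. Omitting such a factor after stratified allocation tends to overstate the standard error and costs precision.

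Nothing here shows that outpatients do worse or that the pooled test is invalid. The probabilities in the working only illustrate how far a pooled pass could hide a deficit in one setting.

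**What to change.** 1. **Section 3.** Limit the schedule sentence to inpatients and state the outpatient schedule beside it, in line with section 2.10. Say that equal session counts remove a dose imbalance only, and that both arms also share therapy to an extent that depends on setting.
2. **Section 2.18.1, primary model.** Add clinical setting, already a stratification factor, as a fixed effect, for precision and correct standard errors.
3. **Section 2.18.1, supportive analysis.** Through a treatment-by-setting interaction, report the treatment difference with its 95% CI for inpatients and for outpatients beside the pooled one. State that this does not replace the pooled non-inferiority test.

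The margin, sample size and data collection stay as they are, because setting is recorded for every patient. The cost is some wording, one model term and two reported intervals. The drawback is imprecision: with an outpatient half-width of about 5 to 8 points against a margin of 5, the outpatient interval will rarely settle non-inferiority in that setting. It can only qualify how far the pooled result is taken to apply.
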